### Study Population

#### Eligibility Criteria

The inclusion criteria for this trial are as follows: both men and women, 18 years and older, will undergo elective cardiovascular procedure such as aortic valve surgery, mitral valve surgery, coronary artery bypass grafting, or any combination of the above procedures. The subjects must have stable renal function with eGFR > 60 ml/min/1.73 m^2^ and creatinine change <0.3 mg/dl in the preceding 1 month prior to scheduled surgery.

The exclusion criteria for this trial are as follows: subjects who

Have ejection fraction of <20% prior to surgeryHave estimated glomerular filtration rate <15 ml/min/1.73 m2 as calculated by Chronic Kidney Disease Epidemiology Collaboration (CKD-EPI) formulaWill have cardiac surgery performed without using cardiopulmonary bypassHave ongoing sepsis or history of sepsis in the last 2 weeks, defined as having 2 of the following criteria: body temperature >38°C or <36°C, pulse rate >90/min, RR >20/min, WBC >12 or >10% polymorphonuclear cells plus a documented sourceHave documented rise in creatinine ≥ 0.3 mg/dl in the preceding 1 month prior to surgeryHave been deemed to have AKI at the time of the surgery by treating clinicianAre on acute or chronic maintenance dialysis at the time of randomizationHave AKI due to glomerulonephritis, thrombotic microscopic angiopathy, obstructive nephropathy, interstitial nephritisAre taking lithium for any conditionsUnable to absorb lithium or take any medications orally.

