To examine the primary endpoint and test the study hypothesis for the effect of lithium on the incidence of AKI, contingency table analysis using chi-square will compare the proportion of AKI within the respective treatment groups. A predictive model that identifies baseline characteristics, including treatment assignment, associated with risk of AKI will be developed. Multivariate testing will use linear regression for continuous outcomes and logistic regression for dichotomous outcomes. Analysis comparing the placebo-control and lithium groups on each baseline characteristic, one at a time, using ANOVA with adjustment for age and sex will be performed. An adjusted logistic regression model based on the dichotomous outcome of occurrence or not of AKI will be further developed to identify characteristics significantly related to AKI. Composite endpoint events, consisting of the first occurrence of AKI, new onset dialysis, and cardiovascular/all-cause mortality, will be compared between treatment groups. Using appropriate uni- and multivariate methods, secondary outcome measures will be incorporated including assessments of renal function/injury such as SCr, NAGL, KIM1, urine TIMP-2, IGFBP7 and [TIMP-2] × [IGFBP-7], urine albumin Cr ratio, as well as indicators of post-operative course including days on mechanical ventilation, days on RRT and infection.

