Stepwise multivariate linear regression analysis will be utilized to examine the independent predictors of changes in renal function over time. The longitudinal effect of lithium on kidney function will be estimated by applying generalized linear mixed model with time (continuous variable) as a random coefficient. The percent change in SCr, NAGL, KIM1, urine TIMP-2, IGFBP7 and [TIMP-2] × [IGFBP-7], and urine albumin Cr ratio at 1 week, 30 days and 60 days will be evaluated. Other covariates identified by univariate analysis or by stepwise selection with Akike information criteria will be included in the model. Additionally, risk factors such as age, diabetes, history of chronic kidney disease (CKD) and dialysis, duration of CPB, aortic cross clamp time, type of surgery (emergent vs. elective), valvular vs. non-valvular and duration of surgery will be examined. All multivariate models will be tested for interaction among predictors. Due to the problem of multiple comparisons, the multivariate modeling will be cautiously interpreted and inference will be regarded as limited, but will be examined for possible hypothesis-generating evidence owing to the multifactorial nature of CSA-AKI.

The primary endpoint is based on the first occurrence within 1 week from surgery of AKI and other composite events described above, therefore time-to-event analysis is limited in assessing risk due to the 1-week AKI criteria from exposure at time of surgery. The hazard associated with outcomes outside of the 1-week threshold, such as death and new onset dialysis, will be examined using time-to-event analysis. The predicted probability of the binary occurrence of these endpoints will be calculated using logistic regression with adjustment for age, sex, and baseline renal function measures. Model performance will be summarized using receiver operating characteristic analysis. Time-to-event for the mortality and dialysis endpoints will be examined using Kaplan-Meier analysis with log-rank estimates to compare the lithium and control groups. Hazard ratios will be calculated using Cox proportional-hazard model adjusted as described above. Model diagnostics using Cox-Snell residual plots for goodness-of-fit, and the null hypothesis of proportional hazard assumption will be tested. The extended Cox model will be used to test for interaction among predictors and time.

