### Sample Size Estimation

To evaluate the effect of the intervention, that is lithium carbonate on improvement of rates of AKI, we will consider rates of AKI in cardiac surgery patients to be about 20% based on prior data (44, 45). A 25% reduction of this rate is considered clinically significant. Cocks and Torgers (46) proposed a sample size calculation for pilot randomized trials based on confidence interval in which the lower limit of one-sided confidence interval (CI) is greater than the clinically significant effect size in order to exclude the estimate that is considered clinically important. Based on the CI approach, a sample size of 182 with 91 in each group is required to produce a one-sided 80% confidence limit that would exclude a 5% difference. The one-sided confidence interval method is being used since we are only interested in proceeding toward a larger trial if there is evidence of efficacy. Because this is a control vs. intervention study design, there is an inherent improvement in the confidence limit since the controls will constrain some of the random error. This sample size agrees with the recommendation of Teare et al. (47), who suggested 60–100 subjects to estimate the event rate in an intervention group and ensures that we will encounter at least one incident at a 99% confidence level (48). Accordingly, a minimum sample size of 58 with 29 in each group is enough to ensure that at least one event would be detected and is a measure of feasibility that the study can detect the clinically significant outcome.

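### The longitudinal lithium effect is estimated with covariates selected on the same data, and the adjusted Cox models planned for dialysis would often be inestimable

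*Protocol article*

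**What the plan says.** All of this is in the protocol article, mostly under Statistical Analysis.

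- **Primary comparison.** For AKI, "contingency table analysis using chi-square will compare the proportion of AKI" between arms, by intention to treat and without covariates.
- **Longitudinal lithium effect.** A generalized linear mixed model with time as a random coefficient estimates lithium's effect on kidney function. Two sentences later: "Other covariates identified by univariate analysis or by stepwise selection with Akike information criteria will be included in the model".
- **Risk factors.** Nine are named. Besides age, diabetes, valvular surgery and duration of surgery, the list has "history of chronic kidney disease (CKD) and dialysis, duration of CPB, aortic cross clamp time, type of surgery (emergent vs. elective". Every multivariate model is to be tested for interactions among its predictors. The paragraph closes by saying that this modelling will be read cautiously and as hypothesis-generating.
- **Dialysis and death.** The next paragraph plans logistic models adjusted for age, sex and baseline renal function, Kaplan-Meier curves with log-rank tests, and then: "Hazard ratios will be calculated using Cox proportional-hazard model adjusted as described above". A test of proportional hazards and an extended Cox model with interactions follow.
- **Eligibility Criteria.** Patients "will undergo elective cardiovascular procedure" and must have "stable renal function with eGFR > 60". A separate exclusion removes eGFR below 15, and another removes patients on dialysis at randomization.

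**The concern.** Three things look wrong.

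First, the mixed model is not only a search for risk factors: it is where lithium's effect on renal function over time is estimated. If its covariates come from univariate screening or stepwise AIC on the trial's own outcomes, nobody can say beforehand which adjusted estimate will be reported, and the printed standard error treats the selected model as if it had been fixed. Randomization makes such selection unnecessary.

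Second, dialysis after cardiac surgery is rare. A Cox model with treatment, age, sex and renal function, then extended with interactions, needs far more events than a trial of this size is likely to see. If one arm has no event, the hazard ratio has no finite estimate.

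Third, a covariate list that contains a factor excluded by eligibility suggests that the two sections describe different populations.

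A lesser point is that the AKI comparison leaves unused the prognostic baseline data that the trial collects anyway.

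**Working it through.** **The plan's own sample size.** Sample Size Estimation states "a sample size of 182 with 91 in each group is required to produce a one-sided 80% confidence limit that would exclude a 5% difference" and, for the rate, "we will consider rates of AKI in cardiac surgery patients to be about 20% based on prior data". With 20% in both arms and z(0.80) = 0.8416:

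n per arm = [0.20×0.80 + 0.20×0.80] × (0.8416/0.05)² = 0.32 × 283.3 = 90.7, so 91 per arm and 182 in total. This reproduces the plan. The minimum of 29 per arm follows from ln(0.01)/ln(1 − 0.15) = 28.3, so 29 per arm and 58 in total.

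**How loose the selection is.** AIC keeps a one-degree-of-freedom term when it lowers the deviance by more than 2. P(χ² with 1 df > 2) = 0.157, so each irrelevant covariate has roughly a 16% chance of being kept.

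**What selection does to the lithium estimate.** The check used a linear model with treatment always kept, nine independent normal candidates, backward AIC, no true treatment effect, a nominal two-sided 5% test and 4,000 simulated trials per setting. The prognostic setting gave three candidates a coefficient of 0.2 residual SD each.

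| N | Candidates | Type I error | Mean SE / true SD of estimate |
|---|---|---|---|
| 182 | all noise | 5.1% | 0.99 |
| 182 | three weakly prognostic | 5.8% | 0.97 |
| 58 | all noise | 6.6% | 0.92 |
| 58 | three weakly prognostic | 7.3% | 0.91 |

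Standard errors are about 1% to 3% too small at 182 patients and 8% to 9% too small at 58. This is a simplification of the planned mixed model and shows only the order of magnitude.

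**Dialysis events.** The protocol gives no planning rate for dialysis. The Introduction cites two cohorts, with 1.4% needing dialysis and 2.7% needing continuous renal replacement therapy. Both are used here as an assumed range, equal in the two arms.

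| Quantity | Rate 1.4% | Rate 2.7% |
|---|---|---|
| Expected events, 182 × rate | 2.5 | 4.9 |
| Events per parameter (treatment, age, sex, one renal measure), divided by 4 | 0.6 | 1.2 |
| P(no event in a given arm), (1 − rate)^91 | 0.277 | 0.083 |
| P(at least one arm has none), 1 − (1 − P)² | 0.48 | 0.16 |
| Expected events at 58 patients | 0.8 | 1.6 |

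The events-per-parameter row is before any interaction term. No mortality rate is given, so the death models cannot be sized in the same way.

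**Covariates against eligibility.** Emergent versus elective surgery cannot vary if only elective surgery is enrolled. The Figure 2 caption names the emergency department among the places where patients are assessed. That does not make the surgery emergent, but it is another reason to align the text. The exclusion at eGFR below 15 removes nobody once eGFR above 60 is required, so the intended renal range is unclear.

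**The case against.** The strongest defence is the protocol's own caveat: multivariate inference is declared limited and hypothesis-generating, with multiple comparisons given as the reason. For the risk-factor search and the interaction tests this is largely a sufficient answer. One could count 45 pairwise interactions among nine factors plus treatment and predict a near-certain false positive. That assumes that every pair is tested independently at 0.05, which the text does not say, and the caveat already covers it. The caveat does not settle which adjusted lithium estimate will be reported, and it cannot make an infinite hazard ratio estimable. It also closes the paragraph before the Cox models are introduced.

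The simulation supports the defence in part: at 182 patients, selection barely disturbs the test of treatment.

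Several stronger readings are tempting but unsupported:

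- **About 32 AKI events, hence about 3 per candidate.** The count is right (91×0.20 + 91×0.15 = 31.9; divided by 10 terms, 3.2), but the stepwise sentence belongs to a longitudinal model of renal function and biomarkers, where AKI events are not the limiting quantity. For the AKI logistic models, data-driven selection is implied by their stated purpose, not by that sentence.
- **Stepwise selection in the dialysis and death models.** Their adjustment set is fixed in advance. Only the sparse-event and interaction criticism applies, and for death it cannot be quantified.
- **CKD and dialysis history ruled out.** Only dialysis at randomization is excluded. A past episode, or a CKD history with eGFR above 60, is unlikely but possible.
- **The unadjusted primary test as an error.** A chi-square test by intention to treat in a 1:1 randomized trial is valid. Adjustment would be a gain in precision, and its size here has not been computed.

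**Conclusion.** The concern holds in a limited form.

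- **Selection in the longitudinal lithium model** is a real defect of specification. Its effect on type I error is modest at 182 patients and more noticeable at 58, on the evidence of a simplified linear model.
- **Adjusted and extended Cox models for dialysis** would often be inestimable: 2.5 to 4.9 expected events, and a 48% to 16% chance of an arm without any. This rests on the Introduction's cohort rates applying equally to both arms with 91 patients each.
- **Emergent versus elective surgery** as a covariate contradicts the elective-only inclusion criterion.
- **The primary test** is sound, and an adjusted estimate would be a worthwhile addition to it.

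Overall severity is minor to moderate. These are mainly secondary analyses, and the protocol labels much of the modelling as limited.

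**What to change.** 1. For the longitudinal lithium model, name a small fixed baseline set in advance, for example age, baseline renal function and valvular versus non-valvular surgery. Delete univariate and stepwise selection and blanket interaction testing from every model that estimates the lithium effect. Keep them, if wanted, only in models labelled as exploratory risk-factor work.
2. Keep the chi-square comparison for AKI, and report beside it a standardised risk difference from a logistic model with treatment and the same baseline set.
3. Report dialysis as counts by arm with exact intervals and a Kaplan-Meier plot. Drop the adjusted and extended Cox models where events are this few, and apply the same rule to death once its event count is known.
4. Remove emergent versus elective surgery from the covariates while inclusion remains elective-only. Reconcile Eligibility Criteria with the risk-factor list, including the eGFR above 60 inclusion with the eGFR below 15 exclusion. Which renal range is intended is for the investigators to state.

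The cost is a change of wording, one additional planned estimate and fewer exploratory models. The baseline variables are already to be collected, and the sample size does not change.

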## Introduction

Cardiac surgery-associated acute kidney injury (CSA-AKI) is a significant problem. The prevalence varies from 0.3 to 22.9% depending on the definition of acute kidney injury (AKI) (1). In a study of 2,222 patients undergoing elective cardiopulmonary bypass (CPB) surgery with or without valvular surgery, 7.7% had AKI, and 1.4% required dialysis (2). Another prospective study by Ostermann et al. of 2,337 patients undergoing cardiac surgery, 2.7% needed continuous renal replacement therapy (3). The etiopathogenesis of AKI in this population is multifactorial (4). Factors associated with AKI in such patients include patient comorbids, procedure related factors, exogenous nephrotoxic agents, hemodynamic insults and genetic factors (5). Mechanism of AKI includes increased afferent arteriolar vasoconstriction leading to ischemic injury. In addition, CPB induces a proinflammatory state, intravascular hemolysis and hemoglobinuria. Although pulsatile flow overall has improved inflammatory response due to reduced leukocyte adherence, in some studies there is no difference in AKI incidence (6). In the initial course the kidney function may still be intact. However, if there is prolonged ischemic, oxidative, and inflammatory injury, further damage will occur leading to renal tubular cell disruption.

CSA-AKI has significant clinical consequences. It is an independent predictor of mortality, morbidity, increased length of hospitalization and costs (7, 8). In a study of over thirty-one thousand patients it was found that a reduction of glomerular filtration rate beyond 30% was associated with 4 times the mortality risk (9). Another retrospective study by Thakar et al. showed that incidence of infections after cardiac surgery was 1.6% in patients without renal failure, 23.7% in patients with renal failure not requiring dialysis, and 58.5% in patients with renal failure requiring dialysis (10). Moreover, these patients were also at increased risk of end stage renal disease in the future (11–13). In another study where AKI was classified according to RIFLE criteria, it was found that survival post cardiac surgery was associated with varying stages of AKI, with 51% at the risk of AKI, 42% having kidney injury, and 26% having kidney failure (14).

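### An ROC summary of the dialysis model would rest on about 3 to 5 events in 182 patients; uncorrected it would be badly optimistic, and corrected it would be too imprecise to use

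*Protocol article*

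**What the plan says.** The last paragraph of Statistical Analysis in the protocol article turns to outcomes beyond the first week, giving death and new dialysis as examples. Besides Kaplan-Meier and Cox analyses it plans a logistic model for each: "The predicted probability of the binary occurrence of these endpoints will be calculated using logistic regression with adjustment for age, sex" and baseline measures of renal function. The number of renal measures is left open, and treatment is not among the covariates named in that sentence. The next sentence is: "Model performance will be summarized using receiver operating characteristic analysis". No validation sample, resampling or optimism correction is mentioned.

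On size, Sample Size Estimation says "a sample size of 182 with 91 in each group is required", and later that "a minimum sample size of 58 with 29 in each group is enough" to see at least one event. On event rates, the Introduction cites one cohort in which "7.7% had AKI, and 1.4% required dialysis", and a second in which 2.7% needed continuous renal replacement therapy. No death rate is given as a planning figure.

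The preceding paragraph of Statistical Analysis asks for caution in reading the multivariate models and treats them as hypothesis-generating. The reason it gives is multiple comparisons.

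**The concern.** An AUC computed on the data that produced the fit is biased upwards, and the bias grows as the number of events falls towards the number of model terms. It needs no variable selection; a fully pre-specified model has it too. With a handful of dialysis events against three or more terms, the fit can largely order the few cases by chance. The trial could then publish a discrimination figure that looks useful although the predictors carry little or no information. The article presents this pilot as preparation for a larger trial, so a figure of that kind is better kept out of its results.

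**Working it through.** **1. The plan's own sample size.** Inputs from Sample Size Estimation: an AKI rate of 20%, a "one-sided 80% confidence limit that would exclude a 5% difference", and 1:1 allocation.

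n per arm = z(0.80)² × [p1(1−p1) + p2(1−p2)] / 0.05². With 20% in both arms: 0.8416² × 0.32 / 0.0025 = 90.7, so 91 per arm and 182 in total, as stated. The minimum of 29 per arm also reproduces: ln(0.01)/ln(0.85) = 28.3, so 29. The totals 182 and 58 can therefore be used as they stand.

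**2. Expected dialysis events.** Rates from the Introduction.

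| Rate | Events in 182 | Events in 58 | Chance of no event in 182 |
|---|---|---|---|
| 1.4% | 182 × 0.014 = 2.5 | 0.8 | 0.986^182 = 7.7% |
| 2.7% | 182 × 0.027 = 4.9 | 1.6 | 0.973^182 = 0.7% |

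The inclusion criteria require eGFR above 60, so dialysis may be rarer here than in the cited cohorts.

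**3. Apparent AUC from noise.** Simulation: 1,500 data sets per setting, 182 patients, a fixed number of events assigned at random, covariates unrelated to outcome (age, sex, one or more renal measures, with or without treatment). Each data set was fitted by maximum-likelihood logistic regression. The AUC was computed on the fitting data and again, with the same coefficients, on fresh data.

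| Events | 3 terms (age, sex, one renal measure) | 4 terms (second renal measure, or treatment) |
|---|---|---|
| 3 | 0.760 | 0.798 to 0.803 |
| 4 | 0.725 | 0.765 to 0.766 |
| 5 | 0.705 | 0.739 to 0.740 |
| 8 | 0.663 | 0.688 to 0.693 |
| 10 | 0.646 | 0.672 to 0.673 |

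The entries are mean AUCs on the fitting data. On fresh data the mean was 0.50 in every setting. With four terms, an apparent AUC of 0.70 or more occurred in 85% of noise data sets at 3 events and in 67 to 68% at 5 events. More terms make it worse: with six, the mean is 0.86 at 3 events and 0.79 at 5.

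The rows for 3 to 5 events describe dialysis. The rows for 8 and 10 events illustrate death and rest on an assumed count.

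**4. Precision of an unbiased AUC.** With m events and n non-events, the standard error under no association is √[(m+n+1)/(12mn)].

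- 3 events, 179 non-events: √[183/(12 × 3 × 179)] = √(183/6444) = 0.17, so a 95% interval of about ±0.33.
- 5 events, 177 non-events: √[183/(12 × 5 × 177)] = √(183/10620) = 0.13, so about ±0.26.

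**5. For comparison, the week-1 AKI model.** At 20% in both arms about 36 events are expected (182 × 0.20 = 36.4), and at 20% versus 15% about 32 (91 × 0.20 + 91 × 0.15 = 31.9). With five noise terms the mean apparent AUC is then 0.61 to 0.62. The optimism is much smaller but not nil.

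**The case against.** The strongest reply is that the fault is read out of silence. The article does not say that the ROC is uncorrected, the lack of a second data set does not rule out cross-validation or the bootstrap, and a condensed article may leave such detail to an analysis plan that is not shown. This stands in part: in-sample ROC is an inference. It does not dispose of the point. The article does fix ROC as the performance measure for these models, and step 4 shows that for dialysis even a perfectly corrected AUC would be uninformative.

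Second, the simulation sets every association to zero. The Discussion lists advanced age, gender and baseline CKD among the factors relevant to AKI, so some real signal is plausible and zero association is a worst case. A reader might infer that whatever AUC this trial reports would be almost wholly overfitting; neither the documents nor the simulation show that.

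Third, a reader might carry the dialysis figures over to death. The documents give no planning death rate, and at an assumed 8 to 10 deaths the noise AUC is lower. Similarly, a single narrow range for dialysis would imply one fixed model, whereas the number of renal measures is open and treatment is not named as a covariate.

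Fourth, a reader might infer that the result would be presented as good discrimination, or used to select patients for the larger trial. Nothing in the article says so. Progression is tied to evidence of efficacy, and caution about multivariate models is promised. That caution concerns multiple comparisons, however, and does not remove this bias.

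**Conclusion.** The point holds for dialysis and, more weakly, for death. For dialysis, the article's own rates imply about 2.5 to 4.9 events in 182 patients. An ROC on the fitting data would then give, from predictors with no association, a mean AUC of about 0.70 to 0.76 (three terms) or 0.74 to 0.80 (four terms) against a true 0.50. This assumes in-sample evaluation, 3 to 5 events and zero association. The imprecision in step 4 does not depend on in-sample evaluation, and is enough by itself to make ROC a poor choice for dialysis. For death, 0.65 to 0.69 with three or four terms is conditional on an assumed 8 to 10 deaths. The models are secondary and exploratory, and the primary chi-square comparison of AKI is untouched. The change is worth making because the misleading figure is predictable and easily avoided.

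**What to change.** - **Dialysis:** remove the ROC summary. Report the number of patients with new dialysis by arm, with confidence intervals.
- **Death:** either remove the ROC summary, or report only a bootstrap optimism-corrected AUC with a confidence interval, labelled exploratory, repeating the whole model-building step in each resample.
- **Week-1 AKI model:** the article names no ROC for it; if an AUC is reported, apply the same correction and label.
- If the analysis plan already contains such a correction, say so in one clause beside the ROC sentence; the dialysis summary should still go.

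The cost is a little more programming in SAS, and a reported AUC that looks less favourable.
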